### Data management and source data

The Biometrics section at UCR is responsible for the Data Management and has written a study specific Data Management Plan and a Data Validation Plan. All data is recorded in the Clinical Report Forms (CRFs) and entered via e-CRF directly into a web-based data capturing system. All CRF data is entered into the e-CRF system by the study coordinators at each site. Study data found in either the hospital records or in the paper CRF is considered to be source data. The source data verification ensures consistency between the e-CRF and the paper CRF/patient hospital file.

### Training

Before the study started, all paramedics and other ambulance personnel at each site were trained in conventional manual CPR according to the 2005 guidelines, in the use of LUCAS™ Chest Compressions System, and in the algorithms of the two different treatments
[13,14]. The training with the LUCAS™ device was supervised by personnel from the sponsor. Retraining for both techniques continues at least every 6 months during the study period. Personnel involved in the study at the emergency department and at other wards inside the hospital are trained according to the requirements at different sites. Training results for both techniques have been monitored once every year in randomly selected personnel (20%–30%) using a modified CPR manikin (Laerdal, Stavanger, Norway) which measures quality of compressions. This training evaluation has been performed and documented annually from 2009 to 2012.

## Discussion

The LINC-study is the first large multicentre trial powered to evaluate short term survival using mechanical chest compressions with the LUCAS™ device compared with manual chest compressions following conventional guidelines
[13,14]. It is being conducted on adult OHCA victims, excluding those who have initial shock success following crew witnessed cardiac arrest or those who have been treated with bystander defibrillation before the arrival of the ambulance service. These groups have a relatively good prognosis. Their exclusion will introduce a negative bias on overall survival in the study, but it will not influence the comparison between the two groups.

The LINC protocol was modified after the Uppsala-Gävle pilot from that originally envisaged in relation to defibrillation strategy
[16]. The study as performed uses shocks without analyse during uninterrupted chest compressions for the first sequence in the LUCAS™ group regardless of underlying rhythm, with increased emphasis of having the device on the patient earlier than in the two previous OHCA studies
[15,16]. The rationale for having this first shock without analyse in the group treated with LUCAS-CPR is to allow earlier possibility of return of coordinated rhythm in patients with VF/VT. Patients with an initial non-shockable rhythm therefore have one unnecessary shock. The possible harm of this has been extensively discussed within the steering committee after careful evaluation of what is known from the literature, but also after discussion with other experts in the field. The consensus reached has been that the shock without analyse has more potential for benefit than for harm. A further cogent reason for both the initial shock without analyse and for giving a shock halfway through other sequences after detection of a shockable rhythm relates to the known need for the perishock pauses to be a brief as possible
[21]. In the LUCAS™ treatment arm, these pauses can be eliminated.

Since no ECG analysis is done before the first defibrillation in the treatment group, a best estimate of the ‘pre-shock ECG rhythm’ is achieved as follows: if a patient has either a pulse or ventricular fibrillation after the first shock, it will be assumed that this patient had ventricular fibrillation before the first shock; if the patient has either asystole or pulseless electrical activity after the first shock, it will be assumed that these patients had the same rhythm before the first shock attempt. ‘Pre-shock’ ECG will be noted in the CRF according to this best estimate.

No other large randomised study using a mechanical chest compression device has been performed or is planned that includes a comparison of injuries from the two different CPR techniques as shown by autopsy
[22-24], which is important when placing any new techniques into a clinical context
[25]. The safety of the LUCAS™ device has been studied only in small randomised studies and these have not shown any significant differences between manual or mechanical chest compressions despite the concerns that have been raised for this type of treatment
[26,27]. A further test of the validity of these results is therefore warranted. It should be noted, however, that even the group randomised to treatment with LUCAS-CPR will have had a period of manual chest compressions before the device was applied, and this could contribute to any injury.

This study has used CPR training intervals similar to those practised in the clinical setting of most EMS in the world, but to ensure quality in both study arms the actual training procedures have been evaluated in randomly selected personnel at each site, as described above.

From spring 2010, the LUCAS™ 1 Chest Compression System was replaced in the study by the LUCAS™ 2 device. This change was made after discussion between the steering committee and the sponsor, and was approved by all of the independent ethics committees. The rationale supporting this decision was that the performance of these two versions of LUCAS™ devices provides mechanical chest compressions with the same rate, depth, duty cycle, and recoil of the chest. This change of device resulted in a few potential benefits for the ambulance crews. They do not need to carry a tank of pressured air, weighing 6.8 kg, which was the power source to LUCAS™ 1. The power source of the LUCAS™ 2 is instead an integrated battery with a weight of 0.6 kg. Secondly, the LUCAS™ 2 is also able to perform chest compressions in 30:2 mode.

During the spring of 2011 the planned interim analysis of the LINC-study was carried out by the Scandinavian Society of Anaesthesiology and Intensive Care Medicine research group. The results of the analysis allowed the study to continue, a decision endorsed by the LINC steering committee. This means that the enrolment continued and the final patient was enrolled in the end of August, 2012, with complete outcome data available 6 month later. The results are expected to be published in a scientific journal during 2013.

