### The LUCAS™ algorithm

Patients randomised to LUCAS™ CPR are treated initially with manual compressions with minimised interruptions until the device is unpacked and ready to use. LUCAS™ is attached to the patient as soon as possible. In this group the defibrillator must be in manual mode. Mechanical compressions are continued initially for 3 min without checking heart rhythm, irrespective of any manual compressions that have been given by bystanders. The sequence is not interrupted for a shock that is delivered during compressions after 90 seconds of this first 3 min cycle, with the remaining 90 seconds of continued compressions to follow. Thus, the first shock is given on the basis only of definite cardiac arrest without knowledge of whether it is or is not ‘shockable’. Subsequently, heart rhythm is determined after each 3 min cycle by interrupting mechanical compressions briefly and never for longer than 10 seconds. If the analysed rhythm is shockable, a new 3 min cycle of compressions is started, incorporating as before one shock delivered after 90 seconds of on-going compressions. If the rhythm is not shockable, a 3 min cycle of compressions without any shock is followed by a new rhythm analysis. Heart rhythm and circulation are checked after each 3 min cycle (Figure
2).

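### The LUCAS-arm pre-shock rhythm is inferred from the state after the first shock, so it depends on outcome and is not comparable with rhythm in the manual arm

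*Protocol article*

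**What the plan says.** The section on the LUCAS algorithm has the first shock delivered 90 seconds into a 3-minute compression cycle, with no look at the rhythm beforehand: "Thus, the first shock is given on the basis only of definite cardiac arrest without knowledge" of whether the rhythm is shockable. The cycle then runs on, "with the remaining 90 seconds of continued compressions to follow", and "Heart rhythm and circulation are checked after each 3 min cycle".

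The Discussion supplies the missing rhythm by a rule. Its reason is specific to one arm: "Since no ECG analysis is done before the first defibrillation in the treatment group". The rule has two parts:

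- A pulse or VF is recorded as earlier VF: "if a patient has either a pulse or ventricular fibrillation after the first shock, it will be assumed that this patient had ventricular fibrillation".
- Asystole or PEA is carried back unchanged: "if the patient has either asystole or pulseless electrical activity after the first shock, it will be assumed that these patients had the same rhythm".

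The result becomes a data item: "ECG will be noted in the CRF according to this best estimate". The text calls it an estimate and an assumption. It does not discuss bias.

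**The concern.** A pre-shock rhythm reads like a baseline fact. Here it is set by what happened after randomised treatment had begun, in one arm only. Three things follow.

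- **Part of the classifier is an endpoint.** A palpable pulse is the first secondary endpoint (Efficacy and safety evaluation). By construction, no LUCAS patient with a pulse after the first shock can be recorded as asystole or PEA.
- **Patients move between classes according to response.** A patient in asystole or PEA who regains a pulse is moved into VF. A VF patient who is in asystole or PEA after the shock is moved out of VF.
- **The rule assumes away a result that the strategy seeks.** The Discussion justifies the unanalysed shock by an earlier return of coordinated rhythm in VF/VT. A VF patient who regains a coordinated rhythm without a pulse is in PEA, and would be recorded as having been in PEA all along.

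If the field were used in a baseline table, a subgroup analysis or an adjusted model, the arms would be compared on a variable that means different things in each.

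**Working it through.** **Timing.** The shock comes at 90 s of a 180 s cycle, and rhythm and circulation are checked at the end of the cycle. Read together, the sections place the classifying observation about 180 - 90 = 90 s after the shock. That the manual arm's rhythm is observed before its first shock is implied by the Discussion; the figure with its algorithm is not shown.

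**Inputs.** The documents give no figure for this rule to reproduce. From the section on sample size I use four-hour survival of 25% (here in both arms, so no device effect) and, for scale, the 6-point difference the trial is powered to detect. The rest are assumptions:

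- v, true VF share: 20, 30, 40%
- S_V, survival in true VF: 40, 50%
- c, share of VF patients in asystole/PEA at the check: 20, 35, 50%, with survival r × S_V, r = 0.4, 0.7, 1.0
- d, share of non-VF patients with a pulse at the check: 1, 5, 10%, with survival p = 60, 80%
- e, share of non-VF patients in VF at the check: 0, 3%, with survival S_N

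**Formulas.**

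- S_N = (0.25 - v·S_V)/(1 - v)
- Recorded VF share: n = v(1 - c) + (1 - v)(d + e)
- Survivors recorded as VF: y = v·S_V(1 - c·r) + (1 - v)(d·p + e·S_N)
- LUCAS survival: y/n in recorded VF, and (0.25 - y)/(1 - n) in recorded asystole/PEA
- The manual arm shows S_V and S_N, so any difference is spurious.

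**Worked case** (v 30%, S_V 50%, c 35%, r 0.4, d 5%, p 80%, e 0):

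- S_N = (0.25 - 0.15)/0.70 = 14.3%
- n = 0.30 × 0.65 + 0.70 × 0.05 = 0.195 + 0.035 = 0.230
- y = 0.15 × (1 - 0.14) + 0.035 × 0.80 = 0.129 + 0.028 = 0.157
- Recorded VF: 0.157/0.230 = 68.3% against 50.0%, +18.3 points
- Recorded asystole/PEA: 0.093/0.770 = 12.1% against 14.3%, -2.2 points

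The recorded VF share is 23% in the LUCAS arm and 30% in the manual arm, so randomisation no longer makes the strata comparable.

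**Variations** (v 30%, c 35%, p 80%, e 0 throughout; differences from unrounded values):

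| S_V | r | d | VF stratum, LUCAS vs manual | Asystole/PEA stratum, LUCAS vs manual |
|---|---|---|---|---|
| 50% | 0.4 | 5% | 68.3 vs 50.0 (+18.3) | 12.1 vs 14.3 (-2.2) |
| 50% | 0.7 | 5% | 61.4 vs 50.0 (+11.4) | 14.1 vs 14.3 (-0.2) |
| 50% | 0.4 | 10% | 69.8 vs 50.0 (+19.8) | 8.8 vs 14.3 (-5.4) |
| 40% | 1.0 | 5% | 46.1 vs 40.0 (+6.1) | 18.7 vs 18.6 (+0.1) |

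**Whole grid** (3 × 2 × 3 × 3 × 2 × 2 × 3 = 648 combinations, all admissible):

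- VF stratum: -5 to +31 points, median +8, favouring LUCAS in 92%. By r: 100% at 0.4, 99.5% at 0.7, 76% at 1.0.
- Asystole/PEA stratum: -7 to +10 points, median -0.5, favouring LUCAS in 42% and against it in 58%. The share favouring LUCAS falls from 75% at d = 1% to 14% at d = 10%.
- Both strata favour LUCAS in 34%.

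These are shares of an assumed grid, not probabilities.

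**Second set of assumptions, to test the sign.** Let VF be 30%, with half of VF patients in asystole/PEA at the check and 3% of non-VF patients with a pulse. Let survival be 70% for non-VF with a pulse and 12% for other non-VF. True non-VF survival is 0.03 × 0.70 + 0.97 × 0.12 = 13.7%. Recorded non-VF survival depends on survival x among VF patients found in asystole/PEA: (0.30 × 0.50 × x + 0.70 × 0.97 × 0.12)/0.829. With x = 35% it is 16.2% (+2.4); with x = 20%, 13.4% (-0.3); with x = 12%, 12.0% (-1.7). The sign turns on a rate that the documents do not give.

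**The case against.** The strongest reply is that no stated analysis uses this variable. The endpoints are not defined by rhythm, the planned Fisher tests carry no covariates, randomisation is stratified by site only, and the exclusions from the predefined population do not mention rhythm. The only stated use is a CRF entry, and how rhythm is analysed may be settled in an analysis plan that is not shown. The article is also open that the value is assumed, and it gives the exact rule. All of this stands. It limits the point to the recorded item and to any later use between arms. It does not remove the point, because the rule itself is written down and records as a pre-shock fact something that was not observed.

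Two stronger readings are tempting. A reader might infer that every rhythm-specific comparison is tilted towards LUCAS, or that both strata show false benefit. The calculations do not support that: the asystole/PEA stratum changes sign within plausible assumptions and is often against LUCAS. A reader might also infer that the main trial result is affected. It is not, since the confirmatory intention-to-treat comparison makes no use of rhythm.

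It is also fair to object that enrolment had ended in August 2012, so collection cannot be changed, and that the observed state may not be fully recoverable, because the recorded VF class merges pulse and VF. The remedy has to work at the analysis stage.

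**Conclusion.** The point holds in limited form. The LUCAS-arm value is post-randomisation, depends partly on an outcome, and is not defined as in the manual arm, so comparisons between arms by recorded rhythm are in general biased. In the recorded-VF stratum the bias favours LUCAS under most of the assumptions tried, with a median of 8 points, which exceeds the 6 points the trial is powered to detect. In the asystole/PEA stratum the direction is uncertain. The sizes rest wholly on assumed rhythm and transition rates. The structural fault does not: it follows from the wording of the rule. It should be corrected before any analysis by rhythm, and it is no threat to the primary result.

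**What to change.** Replace the best-estimate rule in the data definitions:

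- Label the LUCAS-arm value as rhythm/circulation at first check after shock.
- Code pre-shock rhythm as unknown unless it was actually observed before the shock.
- Where only the inferred value was stored, flag it as inferred.
- State that the inferred value will not serve as a baseline characteristic, subgroup factor or covariate in any between-arm analysis, and that any display by it is descriptive only.

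This takes a recode and a few sentences of analysis text, and it changes nothing in treatment. The cost is that no formal rhythm-subgroup comparison is possible unless pre-shock rhythm was obtained the same way in both arms, for example by blinded review of stored pre-shock ECGs if these exist.

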## Conclusion

The LINC-study was designed to evaluate the efficacy and safety of a resuscitation method for OHCA using mechanical chest compressions with the LUCAS™ device associated with defibrillation during compression and to compare the results with those of manual CPR according to 2005 guidelines. As a large randomised multicentre study, it will contribute to knowledge of OHCA and to the role of the mechanical chest compression with LUCAS™.

